## Abstract

**Background:** Gilles de la Tourette syndrome (TS) is a chronic neuropsychiatric disorder characterized by motor and vocal tics. First-line treatments for tics are antipsychotics and tic-specific behavioral therapies. However, due to a lack of trained therapists and adverse events of antipsychotic medication many patients seek alternative treatment options including cannabis. Based on the favorable results obtained from case studies on different cannabis-based medicines as well as two small randomized controlled trials using delta-9-tetrahydrocannabinol (THC), we hypothesize that the cannabis extract nabiximols can be regarded as a promising new and safe treatment strategy in TS.

**Objective:** To test in a double blind randomized clinical trial, whether treatment with the cannabis extract nabiximols is superior to placebo in patients with chronic tic disorders.

**Patients and Methods:** This is a multicenter, randomized, double-blind, placebo controlled, parallel-group, phase IIIb trial, which aims to enroll 96 adult patients with chronic tic disorders (TS or chronic motor tic disorder) across 6 centers throughout Germany. Patients will be randomized with a 2:1 ratio into a nabiximols and a placebo arm. The primary efficacy endpoint is defined as tic reduction of at least 30% (compared to baseline) according to the Total Tic Score of the Yale Global Tic Severity Scale (YGTSS-TTS) after 13 weeks of treatment. In addition, several secondary endpoints will be assessed including changes in different psychiatric comorbidities, quality of life, driving ability, and safety assessments.

**Discussion:** This will be the first large, controlled study investigating efficacy and safety of a cannabis-based medicine in patients with TS. Based on available data using different cannabis-based medicines, we expect not only a reduction of tics, but also an improvement of psychiatric comorbidities. If the cannabis extract nabiximols is proven to be safe and effective, it will be a valuable alternative treatment option. The results of this study will be of high health-economic relevance, because a substantial number of patients uses cannabis (illegally) as self-medication.

**Conclusion:** The CANNA-TICS trial will clarify whether nabiximols is efficacious and safe in the treatment of patients with chronic tic disorders.

**Clinical Trial Registration:** This trial is registered at clinicaltrialsregister.eu (Eudra-CT 2016-000564-42) and clinicaltrials.gov (NCT03087201).

## Introduction

Gilles de la Tourette syndrome (TS) is a common, complex, chronic neuropsychiatric disorder characterized by motor and vocal tics. It causes not only significant impairment in quality of life of the affected patients, but also significant economic costs in the German health care system as a whole (1, 2). The treatment options for chronic tic disorders (CTD) and TS are limited: to date haloperidol is the only approved drug in Germany, which is barely prescribed any more due to severe adverse events (AEs) (3). Instead, most clinicians prefer an off-label use of other antipsychotics such as aripiprazole and risperidone. However, due to AEs and/or lack of efficacy, a substantial number of patients is unsatisfied with this kind of treatment. First-line behavioral therapies (BT) such as Habit Reversal Training (HRT) and Exposure with Response Prevention (ERP) are not available to most patients, because of poor dissemination of these therapy techniques among psychotherapists (3, 4). Therefore, many patients with CTD are looking for complementary and alternative medicine (CAM) including self-medicating with cannabis (5).

Until today only a small number of case studies and series (all together including about 200 patients) is available, reporting about beneficial effects of different cannabis-based medicines including pure delta-9-tetrahydrocannabinol (THC, dronabinol), cannabis extracts, and cannabis flowers in patients with TS. Interestingly, in most of these studies not only a tic reduction is reported, but also an improvement of a broad spectrum of psychiatric comorbidities including attention deficit/hyperactivity disorder (ADHD), obsessive compulsive disorder (OCD), depression, anxiety, rage attacks, sleep disorders, and self-injurious behavior resulting in a significant improvement of patients' quality of life. Most interestingly, in some of these cases, in addition, an improvement of premonitory urges proceeding the occurrence of a tic is described [for review see (6)].

So far only two small randomized controlled trials (including 12 and 24 patients, respectively), have been carried out to further investigate the treatment effects of cannabis-based medicines in patients with TS. In both of these studies pure THC, the most psychoactive ingredient of cannabis, has been used. According to these studies, THC resulted in a tic reduction and was well-tolerated without causing severe AEs or relevant neuropsychological impairment (7, 8).

This study aims to further examine the efficacy and safety of cannabis-based medicines in patients with CTD. At the time, when this study was designed, the only cannabis-based medicines that could theoretically be used in clinical trials in Germany were pure THC, the synthetic THC-analog nabilone, cannabis flowers, and the cannabis extract nabiximols. We decided to use nabiximols, a plant extract from Cannabis sativa L. that contains THC and cannabidiol (CBD) at a 1:1 ratio, for the following reasons: (i) at that time, nabiximols was the only officially licensed cannabis-based medicine in Germany (since 2010 licensed for the treatment of spasticity in multiple sclerosis) (9), (ii) compared to pure THC, it can be assumed that nabiximols – according to the so called entourage effect - is not only more effective [since CBD possesses its own effects (10)], but also better tolerated [since co-administration of CBD mitigates unwanted psychotropic effects of THC (11)], and (iii) compared to herbal products, for most patients preparation, application and intake is easier. Finally, GW Pharma Ltd. kindly agreed to offer nabiximols and placebo as investigational medical product (IMP) for this investigator-initiated study.

The introduction of a prescription of cannabis flowers in Germany in 2017 went along with an intensive and controversial debate on whether treatment with cannabis-based medicines may have a negative impact on patients' driving ability and whether patients should be allowed to drive a car. While in the case of recreational use of cannabis, driving a car is generally not allowed as long as THC tests are positive, the German government stated that in contrast cannabis-based medicines - when prescribed and supervised by a medical doctor - should be handled comparably to other psychoactive drugs (12). This implies that the subject is responsible to accurately self-assess his or her driving ability before using a vehicle. With respect to nabiximols, it has been shown that driving ability is not impaired in patients with multiple sclerosis (13, 14). However, in patients with TS so far only one single case study has been published reporting an improvement of patient's driving ability after treatment with THC (15). To increase our current knowledge regarding the effects of cannabis-based medicines on driving ability specifically in patients with TS, we plan to perform tests of driving ability at baseline and after treatment with nabiximols.

This study is designed as a multicenter randomized double-blind placebo controlled trial using nabiximols compared to placebo. We plan to include 96 adult patients at six large specialized TS centers all across Germany. The effects of nabiximols on tics, comorbidities, and patients' driving ability as well as AEs will be assessed during and after treatment.

## Methods and Analysis

### Drug Information

Nabiximols is a complex botanical mixture derived from the *Cannabis sativa* plant. It contains different cannabinoids and terpenes with THC and CBD being the most abundant cannabinoids present. Nabiximols is a sublingually administered oromucosal spray that contains 10 ml solution in one spray container. The containers have to be stored in accordance with the German legal requirements [German Narcotic Drugs Act (“Betäubungsmittelgesetz,” BtMG)]. Nabiximols and placebo will be manufactured by GW Pharma Ltd., United Kingdom.

### Study Design

This is a multicenter, prospective, randomized, double-blind, placebo controlled, parallel-group, phase IIIb investigator-initiated clinical trial. The time from first patient in to last patient out is expected to be 54 months including a recruitment period of ~28 months. The trial duration per patient will be about 17 weeks, including a 4 weeks up-titration, a 9 weeks maintenance phase, and 4 weeks of follow-up. The study flow is displayed on Figure 1.

**Figure 1 F1:**
[figure not shown]
Study Flow. MS, milestone.

Patients will be randomized to receive nabiximols or placebo with a ratio of 2:1 over the course of a 13-weeks double-blind treatment period. The treatment plan is identical for both treatment arms. In the placebo arm, patients will be treated with a placebo spray identical to nabiximols in visual appearance, taste, and odor. The study design is displayed on Figure 2.

**Figure 2 F2:**
[figure not shown]
Study Design.

### Recruitment

A total number of 96 eligible patients will be included in the clinical trial across 6 participating German study sites. Study participants will be mainly recruited through the study centers' outpatient clinics. In addition, the study will be announced in German self-help and advocacy groups, newsletters and annual meetings. During a screening visit, full information on the study design and the study medication (orally and in writing) will be provided. Before enrollment, a written informed consent will be obtained. Travel costs related to the study participation will be reimbursed. No further financial compensation will be offered.

### Eligibility Criteria

The following inclusion criteria were defined:

TS or chronic motor tic disorder (CMT) according to DSM-5 (CTD = TS + CMT)Age ≥ 18 yearsYale Global Tic Severity Scale – Total Tic Score (YGTSS-TTS) > 14 for patients with TS or YGTSS-TTS > 10 for patients with CMTClinical Global Impression Scale – Severity of Illness (CGI-S) ≥ 4If the patient will be on any medication (or deep brain stimulation) for tics or comorbidities, a stable dose will have to be obtained at least 30 days before entering the study and maintained during the studySigned written informed consentCapacity to understand the investigational nature, potential risks and benefits of the clinical trialWomen of childbearing potential will need to test negative to a beta human chorionic gonadotropin (β-HCG) pregnancy test at screeningBoth sexually active men and women of child-bearing potential will need to agree to use valid methods of contraception.

The following exclusion criteria were defined:

Psychiatric comorbidities in primary need of treatmentOngoing behavioral treatment for ticsHistory of schizophrenia, psychosis, severe personality, or pervasive developmental disorderPresence of suicidal ideation (intent or plan) within the last 12 monthsCurrent diagnosis of substance abuse or dependenceSecondary tic disorders and other significant neurological disordersCurrent or past severe cardiovascular diseases, hepatitis C, or other severe hepatic and renal disordersAny medical condition that might interfere with the patient's participation in the study or pose a risk for the patientUse of cannabis or any cannabis-based medicine in the 30-day period prior to study entry and/or positive THC urine test at baselinePositive pregnancy testPregnancy or lactation periodParticipation in any investigational medication study within 30 days prior to study entry or planned medication change during the study periodKnown or suspected hypersensitivity to any of the active substances or any excipients of the investigational medicinal product.

### Blinding and Randomization

This is a double-blind clinical trial. To prevent unblinding, THC blood tests during the treatment phase will be sent to the laboratory of an unaffiliated institution (University Medical Center Mainz) and the results will be kept confidentially until the end of the study. In addition to examiner and self-assessments for tics, we will use a video-based tic rating as a secondary outcome measure. Since video evaluation will be done centrally by otherwise uninvolved blinded raters, this assessment will be robust against unintentional unblinding.

A permuted block randomization will be used to randomize the treatment allocation in a 2:1 ratio (nabiximols:placebo). Randomization will be conducted centrally and will be stratified by center. We decided in favor of a 2:1 randomization because uneven allocation (i) allows for more safety information in the active treatment group, (ii) enables more precise response rate estimation in the active treatment group, and (iii) facilitates patient recruitment. This study is sufficiently powered for a 2:1 randomization with a power of 90%.

### Compliance

Medication (nabiximols and placebo) will be dispensed to the patients in limited amounts at each clinic visit. Empty spray bottles will be collected at clinic visits. At each clinical visit, a THC urine test will be done to check for compliance with the study medication on the one hand and any concomitant use of cannabis on the other hand (to avoid unblinding, analyses will be done centrally at the end of the trial).

### Active Treatment Phase

The titration phase will last 4 weeks in all patients, independently of the maximum dose and the time for up-titration. The starting dose will be 1 spray/day (= 100 μl spray = 2.7 mg THC/2.5 mg CBD). The standard dose escalation will be the following: For the first 4 days, dose can be increased by 1 spray every 2 days, and thereafter by 1 spray every day up to a maximum dose of 12 sprays/day (= 1,200 μl spray = 32.4 mg THC/30 mg CBD). However, depending on individual tolerability and efficacy slower dose increase is possible. Patients will be allowed to increase their dose to achieve sufficient efficacy in both, the active and the placebo - treatment group to reflect that due to high inter-individual variability different patients may require different doses. Since no target dose is defined, dosage can be increased until the patient reaches his/her individually tolerated maximum dose (1–12 sprays/day) based on the patient's judgment and investigator's assessments. Different dose levels thus reflect different needs of patients with different patient characteristics and not a systematic dose-response investigation. For patients in the placebo arm, titration will follow the same scheme as for nabiximols.

After the 4-weeks titration phase, treatment will be continued at a stable dosage for another 9 weeks. However, dose adjustment will be possible. Thereafter, medication will be withdrawn without down-titration.

### Study Visits and Assessment Instruments

A full assessment schedule for all study and phone visits is given in detail on Table 1.

**Table 1 T1:** Schedule of Study Assessments and Visits.

	**Screening**	**Base-line**	**Titration phase**				**Maintenance phase**				**Follow-up**
**Visit**	1	2	3	4	5	6	7	8	9	10	11
Clinic visits	X	X		X		X		X		X	X
Phone visits			X		X		X		X		
**Week**	−4 to 0	0	1	2	3	4	6	8	10	13	17
**General procedures**											
Written informed consent	X										
Inclusion/exclusion criteria	X										
Demographics	X	X									
Medical & medication history	X	X									
**Laboratory examinations**											
Urine THC	X	(X)^d^									
Blood exocannabinoids and endo-cannabinoids (including THC)		X		X		X		X		X	X
Urine ß-HCG	X	(X)^a^		X		X		X		X	X
**Intervention**											
Randomization	X										
Compliance: asking for compliance			X	X	X	X	X	X	X	X	
**Psychometric assessments**											
Tics: - YGTSS	X	X		X		X		X		X	X
- ATQ		X		X		X		X		X	X
- MRVS		X		X		X		X		X	X
Severity of disease: CGI-S	X	X		X		X		X		X	X
Improvement of disease: CGI-I				X		X		X		X	X
Premonitory urges: PUTS		X		X		X		X		X	X
Quality of life: GTS-QoL		X		X		X		X		X	X
Mood: BDI-II		X		X		X		X		X	X
Anxiety: BAI		X		X		X		X		X	X
ADHD: - DSM-IV symptom list		X									
- WURS-k		X									
- CAARS		X		X		X		X		X	X
OCD: Y-BOCS		X		X		X		X		X	X
Sleep quality: PSQI		X		X		X		X		X	X
Impulsivity: I-8		X		X		X		X		X	X
Patient health: SF-12		X		X		X		X		X	X
Rage attacks: RAQ		X		X		X		X		X	X
**Fitness to drive:**											
- Patient's specific traffic medical history^c^		X^c^									
- Self-assessment for driving ability		X^c^								X^c^	
- Test battery Fa. Schuhfried		X^c^								X^c^	
Evaluation of neurological impairment and impact on driving ability		X		X		X		X		X	X
**Adverse events**											
Open questions			X	X	X	X	X	X	X	X	X
Blood pressure, heart rate		X		X		X		X		X	X
C-SSRS assessment^b^		X		X		X		X		X	X

*THC, delta-9-tetrahydrocannabinol; ß-HCG, beta human chorionic gonadotropin; YGTSS, Yale Global Tic Severity Scale; ATQ, Adult Tic Questionnaire; MRVS, Modified Rush Video-Based Tic Rating Scale; CGI-S, Clinical Global Impression Scale – Severity of Illness; CGI-I, Clinical Global Impression – Improvement Scale; PUTS, Premonitory Urge of Tics Scale; GTS-QoL, Gilles de la Tourette Syndrome-Quality of Life Scale; BDI, Beck Depression Inventory; BAI, Beck Anxiety Inventory; ADHD, Attention-Deficit-Hyperactivity Disorder; DSM, Diagnostic and Statistical Manual of Mental Disorders; WURS-k, Wender Utah Rating Scale; CAARS, Conners' Adult ADHD Rating Scale; OCD, Obsessive-Compulsive Disorder; Y-BOCS, Yale-Brown Obsessive Compulsive Scale; PSQI, Pittsburgh Sleep Quality Index; I-8, Skala Impulsives-Verhalten-8 (measure of impulsivity); SF-12, 12-item short-form Health Survey; RAQ, Rage Attacks Questionnaire*.

a *Only if screening and baseline visit are at least 2 weeks apart*.

b *C-SSRS (Columbia-Suicide Severity Rating Scale): The Baseline version is used at the Screening visit and the Since Last Visit version at all subsequent visits*.

c *In patients not recruited at MHH or LMU, who participate in the study part “Fitness to drive,” variations of the scheduled baseline and follow-up “Fitness to drive” visits are possible*.

d *Only if screening and baseline visit are at least 2 weeks apart*.

#### Assessment Instruments

A test battery will be administered at clinical visits:

Tics: YGTSS (16), Modified Rush Video-Based Tic Rating Scale (MRVS) (17), and Adult Tic Questionnaire (ATQ), a tic self-rating scale, which is parallel in format and content to the Parent Tic Questionnaire (18)Premonitory urges related to tics: Premonitory Urge of Tics Scale (PUTS) (19)Psychiatric comorbidities: Beck Depression Inventory (BDI-II) (20), Beck Anxiety Inventory (BAI) (21), Conners' Adult ADHD Rating Scale (CAARS) (22), DSM-IV symptom list, Wender Utah Rating Scale (WURS-k) (23), Yale-Brown Obsessive Compulsive Scale (Y-BOCS) (24, 25), Rage Attacks Questionnaire (RAQ) (26), Skala Impulsives-Verhalten-8 (I-8) (27), and Pittsburgh Sleep Quality Index (PSQI) (28)Quality of life and overall impairment and severity of disease: Clinical Global Impression-Severity (CGI-S) (29), Gilles de la Tourette Syndrome-Quality of Life Scale (GTS-QoL) (30) and the 12-item short-form Health Survey (SF-12) (31)Safety assessments including the Columbia-Suicide Severity Rating Scale (C-SSRS) Baseline version (32)Driving test “Fitness to drive” (for details see 2.8.2).

In addition, blood will be drawn to measure levels of endocannabinoids and exocannabinoids.

#### Driving Test “Fitness to Drive”

The study part “Fitness to drive” has two main objectives: assessing the driving ability in subjects with TS/CMT in general and investigating the impact of nabiximols on driving ability in this group of subjects. At baseline, therefore, the following additional assessments will be performed: (i) subject's specific traffic medical history, (ii) self-assessment of subjects' general and current driving ability, and (iii) objective assessment of psychomotor skills using The Vienna Test System, a validated, CE-marked and well-established assessment in Germany, which will be carried out in accordance with the German driving license regulations.

“Fitness to drive” is conceived as a dichotomous criterion and is based on the guidelines of the German Federal Highway Research Institute (BASt). A subject will be considered unfit to drive, if he or she has a percent rank below 16 of at least one of the following tests: Reaction time and choice reaction (RT), Stress Behavior capacity (DT-Auslassungen), Stress Behavior performance quantity (DT-Mengenleistung), Concentration (COG), and Perceptual speed (ATAVT).

Data acquisition is carried out during the baseline visit and at visit 10 (after 9 weeks stable treatment) or before discontinuation of the study medication. In addition, at both baseline and follow-up “Fitness to drive” visits, subjects will be asked about their self-evaluation assessment of their general and current driving ability.

For organizational reasons, this study part will be carried out in only two study centers: Hanover (MHH) and Munich (LMU). For patients recruited at other study centers, a participation will be possible (if desired), but will entail additional study visits at MHH or LMU.

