#### Secondary Endpoints

Key secondary analyses will be performed on the continuous YGTSS-TTS changes from baseline with an ANCOVA model adjusted for the baseline YGTSS-TTS and center. Further secondary outcomes are improvements on other clinical variables: YGTSS-Global Score (sum of TTS and global impairment), MRVS, CGI-I, CGI-S, ATQ, GTS-QoL, PUTS, BDI-II, Y-BOCS, CAARS, BAI, PSQI, I-8, SF-12, and RAQ. These measurements are recommended for clinical trials in TS in order to assess the full spectrum of the disease including psychiatric comorbidities and patients' quality of life. Besides the YGTSS-TTS we will use the MRVS - an observational examiner tic assessment - as well as the ATQ, which is a self-assessment scale for tics. In addition, the YGTSS Global score takes into account the overall tic-related impairment on a patient's life, similar to the CGI-I and CGI-S that measure overall clinical impairment and improvement. Finally, the GTS-QoL is used to assess disease specific quality of life. The PUTS is an instrument that measures premonitory urges often preceding the tics. To assess comorbid pathologies, we will use the BDI-II to assess depression, Y-BOCS for obsessions and compulsions, CAARS for ADHD, BAI for anxiety, PSQI for sleep disturbances, I-8 for impulsivity, RAQ for rage attacks, and SF-12 for overall health. Other secondary endpoints are the outcome variables from the study part on driving ability “Fitness to drive.”

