#### Key Secondary Analysis

If the primary null hypothesis will be rejected and superiority of the active treatment over placebo will be demonstrated, non-inferiority of the active treatment compared to placebo will be hierarchically tested regarding the proportion of patients' fitness to drive at the 2-sided significance level of 5% in all patients. The analyses will be done with a Mantel-Haenszel estimate for the risk difference (active treatment minus placebo) stratified by center. If the lower bound of the corresponding 95%-confidence interval is above the non-inferiority margin of −32%, non-inferiority of the active treatment over placebo regarding fitness to drive will be concluded.

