#### Secondary and Safety Analyses

As secondary analysis, we will use YGTSS-TTS change from baseline at 9 weeks of treatment as continuous outcome variable. An ANCOVA will be computed with the covariates: baseline YGTSS-TTS and center. Additionally, a mixed model will be carried out to assess longitudinal changes in YGTSS-TTS (measured by YGTSS-TTS change from baseline to week 4 and week 9). The model will include repeated measures with a first-order autoregressive covariance structure, and include baseline YGTSS-TTS and center as covariates. For this model, the missing values will not be replaced. Further secondary endpoints will be analyzed with the same statistical methods. All secondary analyses are exploratory. Further exploratory analyses may investigate, whether the finally required dose can be related to baseline patient characteristics so that dose recommendations could be given to the patients.

Absolute and relative frequencies of (S)AEs will be calculated for the full analysis set and will be compared between treatment groups by using a chi-squared test.

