## Discussion

### Clinical Implications

This will be the first well-powered controlled clinical trial investigating efficacy and safety of nabiximols in patients with TS/CMT. Thus, this study is not only the very first large controlled study in patients with tic disorders using a cannabis-based medicine, but also the first large controlled trial in a (hyperkinetic) movement disorder in general. Since we will also assess the effects of nabiximols on a variety of psychiatric symptoms (including ADHD, OCD, depression, and anxiety), this study will provide urgently needed data on the potential use of cannabis-based medicines in these conditions (33). This study will be of enormous health-economic relevance, because a substantial number of patients with TS/CMT (but also other psychiatric diseases such as ADHD) uses cannabis as self-medication. However, the current data basis is weak and, therefore, most physicians do not recommend cannabis-based medicines for their patients. Finally, this study will address an important practical question, whether treatment with nabiximols impairs driving ability in patients with TS/CMT.

We hypothesize that nabiximols will be effective not only in the treatment of tics, but also in a large spectrum of psychiatric comorbidities improving patients' quality of life. Accordingly, we expect that patients' driving ability will not be worsened by treatment with nabiximols. If these assumptions are to be proven correct, nabiximols would be a valuable treatment alternative in adult patients with otherwise treatment resistant TS/CMT.

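### The fitness-to-drive non-inferiority test is stratified by center only and leaves out the baseline fitness status that the trial already measures: a loss of precision, not a bias

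*Protocol article*

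**What the plan says.** The section on the driving test defines fitness to drive as a yes/no status. A patient is unfit if "he or she has a percent rank below 16 of at least one of the following tests", and five Vienna Test System measures are listed. The same section and Table 1 place the test battery at baseline and at visit 10, and the Introduction says "we plan to perform tests of driving ability at baseline and after treatment with nabiximols". Testing takes place only in Hanover and Munich. Patients of the other four centers may travel there if they wish.

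Key Secondary Analysis gives the decision rule. Once the primary null hypothesis is rejected, "The analyses will be done with a Mantel-Haenszel estimate for the risk difference (active treatment minus placebo) stratified by center". If the lower 95% bound lies above −32%, "non-inferiority of the active treatment over placebo regarding fitness to drive will be concluded". Baseline fitness status does not appear in the rule.

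Secondary Endpoints adds: "Other secondary endpoints are the outcome variables from the study part on driving ability". Secondary and Safety Analyses says: "Further secondary endpoints will be analyzed with the same statistical methods. All secondary analyses are exploratory". The methods meant there include an ANCOVA on baseline value and center.

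**The concern.** The visit-10 status is likely to be correlated with the same status at baseline, because the same patient takes the same tests against the same cut-off. A comparison that ignores such a baseline value carries variance that the trial has already paid to measure. In a non-inferiority test this widens the interval, so a harmless drug more often fails to clear the margin. It matters most if few patients take the driving tests, which is possible because this study part is mandatory only for a subgroup at two of the six sites. The plan already adjusts its continuous tic outcome for baseline, but not this test.

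**Working it through.** **The plan's own figures.** The article states no power or sample size for the driving test. Its only sample-size figure concerns the tic responder endpoint. That figure reproduces: an exact Fisher test with 0.025 in each tail, response rates 0.294 v 0.010 and 2:1 allocation gives power 0.917 at 50 + 25 and 0.899 at 48 + 24. The enrolled 64 + 32 is therefore taken as the upper limit for the driving test, and 32 + 16 as an assumed lower participation.

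**Inputs.**
- From the article: cut-off at percent rank 16 (z = −0.994), any of five tests, margin −0.32, two-sided 95% interval, 2:1 allocation.
- Assumed: norm-like scores, equal between-test correlation 0.3–0.7, retest correlation 0.5–0.7, no center effect.
- Consequence: patients who match the norms would be unfit in 48%, 42% and 35% of cases at between-test correlations of 0.3, 0.5 and 0.7, so about 52–65% would be fit.

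**Closed-form check at one setting.** Take between-test correlation 0.3 and retest correlation 0.6. The proportion fit is p = 0.52, and the correlation between baseline and visit-10 status is φ = 0.342.

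- Unadjusted: SE = √[p(1−p)(1/n₁ + 1/n₂)]
- Adjusted for baseline status: SE × √(1−φ²), with 1−φ² = 1 − 0.117 = 0.883
- Chance of concluding non-inferiority with no true difference: Φ(0.32/SE − 1.96)

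64 v 32:
- Unadjusted SE = √(0.2496 × 0.046875) = 0.1082; Φ(2.957 − 1.96) = Φ(0.997) = 0.84
- Adjusted SE = 0.1082 × 0.940 = 0.1016; Φ(3.150 − 1.96) = Φ(1.190) = 0.88

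32 v 16:
- Unadjusted SE = √(0.2496 × 0.09375) = 0.1530; Φ(2.092 − 1.96) = Φ(0.132) = 0.55
- Adjusted SE = 0.1530 × 0.940 = 0.1438; Φ(2.225 − 1.96) = Φ(0.265) = 0.60

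Simulation of the same setting gave 0.847 and 0.875 at 64 v 32, and 0.546 and 0.597 at 32 v 16. The variance ratio of 0.883 is worth about 96/0.883 ≈ 109 patients in place of 96.

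**Simulation over the assumed range**, adjusted analysis as a Mantel-Haenszel risk difference in test site × baseline fitness strata:

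| Non-inferiority concluded | without baseline status | test site × baseline fitness |
|---|---|---|
| No true decline, 64 v 32 | 84–90% | 86–95% |
| No true decline, 32 v 16 | 55–62% | 59–71% |
| 0.5 SD decline on all tests, 64 v 32 | 11–17% | 12–19% |

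In the last row the true loss in the proportion fit is about 21–25 points, inside the margin.

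**Why test site and not six centers.** Crossing baseline status with six centers makes twelve strata. At 32 v 16 with no true decline the chance then goes from 56–60% to 53–67%, with little or no gain when the retest correlation is 0.5. Two sites × two statuses makes four strata.

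**The case against.** The strongest defense is that nothing here is wrong. The dichotomy is deliberate and follows a national guideline. Stratifying by center matches the center-stratified randomization. The risk difference is valid without a baseline term. Every psychometric input above is assumed. If most patients are fit, there is also less to gain: at a proportion fit of 0.8, the unadjusted closed-form chance at 64 v 32 is already 0.96. All of this stands, and it is why the point concerns precision only.

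That the full analysis plan may say more does not settle it, because the article does not leave the stratification open; it names center and nothing else.

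A reader might infer something stronger: that the any-of-five rule is too blunt for a safety question, so the trial could declare driving unharmed while its own scores fall. The documents do not support this.
- The conclusion in Key Secondary Analysis is worded narrowly, as fitness to drive. In Clinical Implications, "whether treatment with nabiximols impairs driving ability in patients with TS/CMT" is a question and "we expect that patients' driving ability will not be worsened by treatment with nabiximols" an expectation; neither is a decision rule.
- Secondary Endpoints and the analysis section together already imply an exploratory, baseline-adjusted analysis of the driving variables.
- A pass alongside a significant fall in scores is mostly a correct decision when the true loss lies inside 32 points. Non-inferiority and some decline above zero can both be true.

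A rule that limits the conclusion whenever a score interval lies below zero would have no threshold of clinical relevance. It is an optional reporting choice and not part of this point.

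**Conclusion.** The point holds as a modest, avoidable loss of precision in the one driving test that carries a decision rule. There is no bias, no contradiction and no fault in the guideline criterion. With no true decline, the gain from using baseline status is roughly 2–6 percentage points at 64 v 32 and 4–9 points at 32 v 16, comparing the ends of the ranges. These figures rest on assumed norm-like scores, assumed between-test and retest correlations, no center effect and an unknown number of tested patients. They apply to the driving test once it is reached, since it is opened only by primary success. The change is worth considering; the trial's validity does not depend on it.

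**What to change.** In Key Secondary Analysis, replace stratification by center with: Mantel-Haenszel risk difference stratified by baseline fitness status (fit/unfit) and driving-test site (Hanover/Munich). Fix this before unblinding and not as a fallback for sparse strata, so that no data-dependent choice enters the hierarchical test. Keep the endpoint and the −32% margin.

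Cost: one sentence, with no new visits, patients or measurements. There are three downsides.
- Center is coarsened from recruiting center to test site, so the analysis no longer mirrors the randomization strata exactly.
- A patient without a baseline driving test cannot be placed in a stratum, so the handling of such patients must be stated in advance.
- With a true decline inside the margin a pass becomes slightly more likely, as the 0.5 SD row of the table shows.
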